### Informed consent procedures 26a

Patients will be informed about the benefits and risks of the current trial. Subsequently, the principal investigator ([name]) will explain the study’s purpose to the patients and obtain their written informed consent before they participate.

### Additional consent provisions for collection and use of participant data and biological specimens {26b}

The consent form provided to participants includes their agreement to use the data in future studies related to this one. However, they are not obligated to consent to any other studies beyond this.

### Interventions

#### Explanation for the choice of comparators {6b}

While receiving standard treatment, patients will be assigned to one of two groups: a treatment group receiving an inulin supplement or a control group receiving a placebo. The treatment group will receive one pack containing 10 g of inulin per day, while the control group will receive one placebo pack containing 10 g of maltodextrin per day for a duration of 12 weeks. Previous studies have shown that supplementation with 10 g of inulin per day is safe and does not cause any serious side effects [39, 40].

#### Intervention description {11a}

Upon recruitment into the trial, patients will be randomly assigned to one of two groups. The intervention group will receive one pack of 10 g inulin (Frutafit® TEX, Sensus; DP ≥ 23) daily for 12 weeks. The control group will receive one placebo pack containing 10 g maltodextrin (Zarfructose Company; dextrose equivalent [DE] = 14) daily. Maltodextrin was chosen as the placebo because it is easily digested and has a similar appearance and taste to inulin. Inulin and placebo will be packed with the same shape, color, weight, and size. A person who is unaware of the study details will label the packs containing inulin and maltodextrin as A or B. Patients will be instructed to continue their usual diet, physical activity, and medications until the intervention is completed. They will also be given instructions on how to use their supplements. Every 4 weeks, patients will receive packs of inulin and a placebo. Additionally, weekly follow-up phone calls and clinic visits will be used to evaluate side effects and treatment compliance.

#### Criteria for discontinuing or modifying allocated interventions {11b}

Patients may withdraw from the trial at any time for any reason. The investigator may withdraw patients from the trial to protect their safety or if they are unable or unwilling to continue with the trial. Furthermore, the reasons for each patient’s withdrawal from the trial will be explained in detail in the study results.

#### Strategies to improve adherence to interventions {11c}

Patients will be provided with inulin and placebo packs at weeks 1, 4, and 8. At the baseline, each phone call, and intermediate visits, all patients will receive instructions on how to use their supplements. They will be requested to return the packs with any remaining contents at the end of each 4-week period, and any side effects experienced will be recorded. Additionally, patients will be asked to complete a daily calendar immediately after consuming their assigned treatments. Adherence to intervention refers to the extent to which trial participants’ behavior aligns with their assigned intervention. Adherence to the assigned treatments will be assessed through the use of a daily calendar during each phone call and by counting the returned packs at the end of the trial. Compliance will be calculated using the following formula: Compliance rate = (packs taken / packs prescribed) × 100. A compliance rate below 80% will be classified as poor compliance.

#### Relevant concomitant care permitted or prohibited during the trial {11d}

Patients will receive standard care and treatment from a specialist doctor, which will not be altered during the study. In addition to their regular treatments, patients will only receive inulin supplements or a placebo. There are no restrictions on appropriate concurrent care for participants, who are also allowed to maintain their regular care.

### Provisions for post-trial care {30}

Standard treatments will continue after the trial concludes; however, placebo or inulin supplements will only be administered for a duration of 12 weeks during the trial.

### Outcomes {12}

This study will be conducted as a randomized double-blind placebo-controlled clinical trial to investigate the effects of inulin supplementation on clinical symptoms, inflammatory status, oxidative stress, intestinal permeability, mental health, and QOL in women with migraine. The primary outcome of this study is to evaluate the impact of inulin on the frequency of headaches in women diagnosed with migraines. In addition to this, the study will also focus on secondary outcomes, which include the assessment of serum levels of zonulin, Hs-CRP, total antioxidant capacity (TAC), total oxidant status (TOS), and NO. Furthermore, the mental health status, QOL, duration, and severity of migraine attacks will also be evaluated. The migraine symptoms, such as headache frequency, severity, and duration will be assessed by a neurologist. Participants will then be asked to complete questionnaires regarding the duration and frequency of the attacks during the intervention. The frequency of attacks will be recorded by the monthly incidence of headaches. The severity of pain will be assessed using a visual analogue scale (VAS) ranging from 0 to 10. Participants will be instructed to score 0 if they experience no pain and 10 if they suffer from agonizing pain. The study will measure the following parameters at the baseline and the end of the intervention: levels of zonulin, Hs-CRP, NO, TAC, and TOS, clinical symptoms, mental health status, and QOL. Blood samples will be collected from the patients both before and 12 weeks after the intervention with either inulin or placebo. These samples will be drawn in the morning (8–10 am) under fasting conditions. Following collection, serum will be separated from the blood samples through centrifugation and then aliquoted into 0.5-ml microtubes. The serum samples will subsequently be stored at − 70 °C in a freezer until further analysis.

### Participant timeline {13}

The protocol flow chart and timeline of the study are illustrated in Fig. 1 and Table 1, respectively. The study protocol was designed and developed in accordance with the Standard Protocol Items: Recommendations for Interventional Trials (SPIRIT) 2013 checklist (Additional file 1, SPIRIT Checklist).

**Fig. 1 Fig1:**
[figure not shown]
The protocol flow chart and timeline of the study

**Table 1 Tab1:** Schedule of enrollment, intervention, and assessment based on SPIRIT guidelines

		Registration	Allocation	Post-Allocation												Close-out
Time point (week)		-W_1_	W_0_	W_1_	W_2_	W_3_	W_4_	W_5_	W_6_	W_7_	W_8_	W_9_	W_10_	W_11_	W_12_	W_13 (starting)_
Registration	Eligibility testing	*														
	Informed consent	*														
	Randomization		*													
	Allocation		*													
	Patient instruction			*												
Intervention	Supplementation			*	*	*	*	*	*	*	*	*	*	*	*	
	Compliance			*	*	*	*	*	*	*	*	*	*	*	*	
	Adverse events			*	*	*	*	*	*	*	*	*	*	*	*	
Assessment	Demographic			*												*
	Anthropometric indices			*												*
	Physical activity			*												*
	Dietary intake			*												*
	Mental status			*												*
	Quality of life			*												*
	Clinical features			*												*
	Biochemical assays			*												*
	Supplement checklist															*

Demographic variable including: type of migraine (episodic and chronic), age, anthropometric indices, education status (university graduated, and non-university graduated), marital status (single and married), migraine in first relatives, gastrointestinal problems (bloating, constipation and diarrhea), medication (beta-blockers, anticonvulsant drugs, Tricyclic Antidepressants (TCA), Tetracyclic Antidepressant (TeCA), Serotonin-Norepinephrine Reuptake Inhibitor (SNRI) or mixture of them); Anthropometric indices including: body weight (BW), body mass index (BMI) and waist circumference (WC); Mental including: depression, anxiety, stress; Quality of life including: migraine Specific Quality of Life (MSQ) and the headache impact test-6 (HIT-6); Clinical features including: frequency, severity, duration; Biochemical assays including: serum zonulin, High-sensitive C reactive protein (Hs-CRP), total antioxidant capacity (TAC), total oxidant status (TOS), nitric oxide (NO)

### Sample size {14}

The sample size for the present study was calculated based on means and standard deviations for the frequency of attacks, as the main outcome of the study of Ghavami et al. [41], by considering a 95% confidence interval and 80% power (*α* = 0.05 and *β* = 0.2). Frequency of attacks was also considered a main outcome, and based on a previous study, the sample size was calculated as 40 patients for each group. All patients who meet the inclusion criteria and are willing to participate in the trial will be included until the estimated sample size is completed.

### Recruitment {15}

The participant composition will consist of 80 patients with migraine recruited from a neurology clinic affiliated with Isfahan University of Medical Sciences in Isfahan, Iran. Our recruitment methods include in-person visits and written materials (such as flyers and brochures). We direct all interested and potential volunteers to a neurologist who will check their eligibility criteria. We obtain written informed consent from all eligible participants who voluntarily join the study. Patients who meet the ICDH-3 criteria [42] for diagnosing migraine will be assessed for eligibility criteria. An expert neurologist ([name]) will then differentiate migraine from other types of headaches such as tension-type headache (TTH), trigeminal autonomic cephalagia (TACs), medication overuse headache (MOH), cluster headache (CH), and headache due to menstrual cycle.

### Migraine diagnosis

According to the ICHD-3, a neurologist will diagnose migraines. ICDH-3 is a well-known and up-to-date diagnostic instrument used in clinical research for headaches. Based on the ICDH-3 criteria, an individual must have at least five attacks that fulfill criteria A–C:

A)Headache attacks lasting 4–72 h (when untreated or unsuccessfully treated)B)Headache with at least two of the following four characteristics:Unilateral locationPulsating qualityModerate or severe pain intensityAggravation by or causing avoidance of routine physical activity (e.g., walking or climbing stairs).C)During a headache, at least one of the following:Nausea and/or vomitingPhotophobia and phonophobia

### Assignment of interventions: allocation

#### Sequence generation {16a}

The present study will be conducted as a randomized double-blind, placebo-controlled study using a stratified randomization method. Stratified permuted block randomization will be employed to balance age (20–35 and 35–50 years) between the two groups over time. Within each of the aforementioned strata, eligible patients will be randomly assigned in a 1:1 ratio to receive either inulin or placebo with a block size of four. A block size of four will be constructed in six different arrangements (blocks) which will be created for each stratum to assign patients to the trial groups. The sequence of these blocks will be generated for each stratum using a random number generator available at randomizer.org. A person not involved in the study will randomly divide patients into two groups: intervention (inulin, *n* = 40) and control (placebo, *n* = 40).

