### Eligibility criteria {10}

#### Inclusion criteria

The inclusion criteria will consist of patients who meet the following conditions:Aged between 20 and 50 years with a diagnosis of migraines by a neurologist ([name]), based on the International Classification of Headache Disorder-3 (ICDH-3)Residents of Isfahan city who are willing to participate in the studyFill out a written informed consent form prior to participation in this trial

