### Statistical methods

#### Statistical methods for primary and secondary outcomes {20a}

Statistical analyses will be conducted using SPSS (version 21.0) software. A *P*-value < 0.05 will be considered statistically significant. The one-sample Kolmogorov–Smirnov test will be used to evaluate the normality of the distribution of data. Regarding missing values, the data analysis will be subjected to intention-to-treat (ITT) analysis. We will employ the multiple imputation approach to perform ITT. In order to compare the baseline value of qualitative and quantitative variables, the chi-square test and *t*-test will be used. Categorical variables will be expressed as number and percentage, while quantitative data will be presented as mean ± standard deviation. Between-group differences will be evaluated using a Mann–Whitney *U* test and independent *t*-test. Differences within the group will also be assessed with a Wilcoxon rank-sum test and paired *t*-test. To control for confounders, an analysis of covariance (ANCOVA) will be carried out.

The primary results of this study include the evaluation of clinical symptoms of patients, such as headache frequency, duration, and severity. The secondary results encompass the evaluation of the serum levels of zonulin, Hs-CRP, TAC, TOS, NO, mental health status, and QOL by questionnaire.

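### The age strata overlap at 35, and, as a separate matter, the stated between-group comparison does not name the randomisation stratum; both effects are small and cheap to put right

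*Protocol article*

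**What the plan says.** In the protocol article, Sequence generation {16a} sets the strata: "Stratified permuted block randomization will be employed to balance age (20–35 and 35–50 years) between the two groups over time". Within each stratum, "eligible patients will be randomly assigned in a 1:1 ratio to receive either inulin or placebo with a block size of four". Each stratum has its own list: "The sequence of these blocks will be generated for each stratum using a random number generator available at randomizer.org". The inclusion criteria admit patients "Aged between 20 and 50 years with a diagnosis of migraines by a neurologist", so age 35 is eligible. No section says whether a 35-year-old belongs to the younger or the older list.

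Statistical methods for primary and secondary outcomes {20a} states the comparison of the groups: "Between-group differences will be evaluated using a Mann–Whitney *U* test and independent *t*-test". It then adds: "To control for confounders, an analysis of covariance (ANCOVA) will be carried out". No covariate is listed. Neither age nor the randomisation stratum is named as a term in any analysis.

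**The concern.** There are two points, and they do not depend on each other.

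First, a separate block list per stratum works only if every eligible patient belongs to exactly one stratum. As printed, a 35-year-old belongs to both. Which list she is drawn from is then left to whoever handles the allocation. Her stratum also cannot be rebuilt from her age afterwards; it has to come from the allocation record.

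Second, stratified blocks force the two arms to be nearly equal on age band. That removes part of the chance variation in the difference between the arms. A t-test or Mann–Whitney test does not know this and still counts the variation between age bands as noise. If age band predicts headache frequency, the unadjusted standard error is somewhat too large for the design, and some of the benefit of stratifying is given away. What is at stake is a small amount of power in a trial of 80.

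**Working it through.** **Number of women affected by the overlap.** The inclusion criteria allow ages 20 to 50, which is 31 completed years of age. The document gives no age distribution, so assume an even spread. The expected number aged 35 is 80 / 31 = 2.6, that is about 2–3 women. An uneven spread would change this.

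**The planned sample size, for reference.** Sample size {14} gives 40 per group, "by considering a 95% confidence interval and 80% power". The mean difference and SD are in a cited study that is not shown, so 40 cannot be reproduced forwards. Solved backwards with a two-sided test (sidedness is not stated), the standardised difference is (1.960 + 0.842) / √(40/2) = 0.626. This figure is not in dispute; it serves only as the effect for the power comparison.

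**Effect of leaving the stratum out.** Let R² be the share of outcome variance explained by age stratum. With the arms balanced within strata, the unadjusted standard error is too large by a factor of about 1 / √(1 − R²):

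- R² = 0: 1.000
- R² = 0.05: 1 / √0.95 = 1.026
- R² = 0.10: 1 / √0.90 = 1.054

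The document does not give R². The range 0 to 0.10 is an assumption, and 0.20 is shown below only as an outer case.

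**Simulation of the stated design.** 80 patients, two strata, blocks of four, 1:1, normal outcome, 20,000 runs per setting, with 50% or 30% of women in the older stratum. The unadjusted t-test is compared with a linear model containing the stratum. Ranges cover the two stratum shares; power is at a standardised difference of 0.626.

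| R² | SE ratio, unadjusted / adjusted | Type I error, unadjusted | Type I error, adjusted | Power, unadjusted | Power, adjusted |
|---|---|---|---|---|---|
| 0 | 1.000 | 4.9% | 4.9–5.0% | 78.6–79.0% | 78.6–79.0% |
| 0.05 | 1.026 | 4.5% | 5.0–5.1% | 79.0–79.9% | 80.4–81.4% |
| 0.10 | 1.055 | 3.9–4.0% | 5.0–5.1% | 79.5–79.9% | 82.3–82.8% |
| 0.20 | 1.119 | 2.9–3.1% | 4.9–5.2% | 80.8–81.3% | 86.7–86.9% |

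The simulated ratios agree with the formula. The unadjusted test never exceeds its nominal 5%. Naming the stratum gains about 1.5 percentage points of power at R² = 0.05, about 3 at R² = 0.10, and nothing if age is unrelated to headache frequency.

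**The case against.** **The overlap may be only notation.** If the cut is made on exact age, two bands meeting at 35 touch at a single point, and the team may have applied one rule throughout. That is possible, but the text does not say so, and a list rule has to be fixed before allocation. The request for clarification stands.

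**A reader might infer that concealment is broken for 35-year-olds.** The reasoning would be this. In a block of four, the fourth assignment is always fixed by the first three, and the third is fixed in 2 of 6 arrangements. So (1 + 1/3) / 4 = 1/3 of assignments are known, as A or B, to someone who has seen the earlier letters. With a free choice between two lists, the chance that at least one next letter is known is 1 − (2/3)² = 5/9, if block positions are random and independent. The document does not support that conclusion. It provides opaque sealed envelopes that conceal the sequence from those who assign, an independent coordinator, and packs of identical appearance. Knowing a letter is not the same as knowing the product. The predictability comes from the fixed blocks and the two pack codes, which apply to all 80 women whatever the age bands.

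**A reader might infer that the overlap makes the error bars wrong.** It does not. The standard-error point arises from leaving out the stratum and would be the same with exclusive bands.

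**A reader might infer that the analysis ignores age altogether.** That is too strong. The ANCOVA covariates are left open and could include age or the stratum, and a covariate list is commonly left to the analysis plan, which is not shown. This part of the objection stands: the missing list is not a fault in itself. What remains is that the article does state a between-group comparison, that this comparison is unadjusted, and that a better one is available.

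**The loss is small and assumed.** This also stands. Moreover, once baseline frequency is in the model, the relevant R² is what age adds beyond baseline, which may be less.

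**Conclusion.** Both points hold in a limited form.

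(1) The bands overlap at age 35 and no rule resolves it. The ambiguity is small, about 2–3 of 80 women under an assumed even age spread. It does not bias the comparison or change the standard errors, provided the list is chosen without knowledge of the next assignment.

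(2) The stated tests do not use the randomisation stratum, and the ANCOVA does not name it. Over an assumed 0–10% of outcome variance explained by age stratum, the unadjusted standard error is about 0–5% too wide. The error is in the conservative direction: type I error falls from 5% to about 4% at most within that range, and up to about 3 points of power are given up. There is no mismatch if age is unrelated to headache frequency.

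Neither point threatens the validity of a positive result. The first is a certain misstatement of small consequence. The second is an improvement available at almost no cost.

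**What to change.** **Strata.** Recruitment began on August 21, 2023, before protocol version 3.0 of September 17, 2023, so the bands should describe what was done rather than set a new rule. State exclusive bands in completed years that match the rule actually applied, whether 20–34 and 35–50 or 20–35 and 36–50. Record, for each 35-year-old already randomised, the list from which her allocation came. If practice was mixed, say so and keep the list actually used as her stratum.

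**Analysis.** Make the ANCOVA of week-12 headache frequency the primary between-group comparison in place of the unadjusted tests. Its covariates should be baseline frequency and the age stratum used at randomisation.

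**Cost.** A clarified line in the sequence-generation section, a check of the allocation records for a handful of women, and two named covariates. Baseline frequency and age are already collected, so no extra patients or visits are needed. The protocol's own amendment section requires ethics committee approval and a registry entry if the change counts as one that may affect the trial's implementation. The analysis change should be fixed before the codes are opened.

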## Methods: participants, interventions, and outcomes

### Study setting {9}

This clinical trial will be carried out at the neurology clinic affiliated with Isfahan University of Medical Sciences in Isfahan, Iran.

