#### Concealment mechanism {16b}

To ensure blinding, packs of inulin or placebo will be labeled as A and B by an independent person who is not involved in the trial. Both patients and investigators will be unaware of the treatment assignment. The allocation sequence will be concealed from those assigning patients to the intervention groups using opaque sealed envelopes. Randomization codes will only be unlocked after all participants have completed the trial protocol.

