#### Implementation {16c}

An independent clinical research coordinator will assign patients to either the intervention or placebo group. The generation of the allocation sequence for patients will be monitored by a second researcher ([name]).

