### Oversight and monitoring

#### Composition of the coordinating center and trial steering committee {5d}

The researchers and all aspects of the study will be supervised by the Ethics Committee and the Vice-Chancellor of Isfahan University of Medical Sciences, who will ensure that the study adheres to ethical principles and protects the patient’s health and dignity. In case of any ethical violations, the study may be corrected or terminated. The principal investigator is the lead researcher and main coordinator of the trial. The principal investigator and research physician are in charge of recruiting, treating, and following up with participants. A steering committee will oversee the entire study process. The study team will also communicate regularly to monitor progress.

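### A fixed, disclosed block of four with only two trial-wide pack letters makes about one third of upcoming letters certain to anyone who knows the earlier ones, and the article does not keep those letters from recruiting staff

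*Protocol article*

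**What the plan says.** Sequence generation {16a} fixes one block size: "eligible patients will be randomly assigned in a 1:1 ratio to receive either inulin or placebo with a block size of four". It adds that "A block size of four will be constructed in six different arrangements (blocks) which will be created for each stratum", and gives the strata: "Stratified permuted block randomization will be employed to balance age (20–35 and 35–50 years) between the two groups over time". The total is 80 women, 40 per arm.

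There is one site (Study setting {9}): "This clinical trial will be carried out at the neurology clinic affiliated with Isfahan University of Medical Sciences".

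Intervention description {11a} and Concealment mechanism {16b} have every pack labelled with one of two letters, A or B. The same two letters serve the whole trial. Packs are supplied every four weeks, and women hand back what remains at the end of each such period (Strategies to improve adherence {11c}).

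On roles, the section on the coordinating center and steering committee {5d} states: "The principal investigator and research physician are in charge of recruiting, treating, and following up with participants".

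The stated safeguards are these. Concealment mechanism {16b}: "The allocation sequence will be concealed from those assigning patients to the intervention groups using opaque sealed envelopes". Implementation {16c} gives assignment to an independent coordinator. Patients and investigators are to be unaware of treatment, and the two products are packed to look alike.

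**The concern.** An opaque envelope hides the next allocation only from someone who cannot work it out from those already made. In a block of four with two of each letter, the fourth letter always follows from the first three, and the third follows from the first two when they match. The block size is fixed and written down, there is one clinic, and only two lists have to be followed. Counting is therefore easy for anyone who can read the letter on earlier women's packs.

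Allocation concealment is meant to stop knowledge of the next assignment from influencing who is enrolled and when. The independent coordinator makes the assignment, but recruiting lies with the principal investigator and research physician, who also follow the women up. The primary outcome is headache frequency, and its baseline level can be known at recruitment. If a recruiter who knows the next letter holds back or brings forward a woman with frequent attacks, the arms can differ at baseline in the very quantity that the trial measures.

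**Working it through.** **Inputs from the protocol article.** Block size 4, 1:1, six arrangements, two age strata, 80 women (Sequence generation {16a}); one clinic (Study setting {9}); two letters for all packs (Concealment mechanism {16b}).

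**Assumption.** The observer knows every earlier letter in order, each woman's stratum and the block size.

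**The plan's own figure.** The number of orderings of two A and two B is C(4,2) = 6, which agrees with the article.

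**Certain letters.**
- AABB and BBAA: after two equal letters the last two are certain, so 2 certain places each.
- ABAB, ABBA, BAAB and BABA: only the last is certain, so 1 each.
- Mean per block: (2×2 + 4×1)/6 = 8/6 = 1.33 of 4, or 33.3%.
- By place in the block, the chance that the letter is certain is 0, 0, 1/3 and 1.

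**Over 80 women.**
- Both strata end on full blocks: 20 × 4/3 = 26.7.
- Last blocks filled to 1 and 3: 19 × 4/3 + 0 + 1/3 = 25.7.
- Last blocks filled to 2 and 2: 19 × 4/3 + 0 = 25.3.
- The range is about 25 to 27.

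**Best guess.**
- Place 1: 1/2.
- Place 2: 2/3, because two of the three remaining letters are the other one.
- Place 3: 1/3 × 1 + 2/3 × 1/2 = 2/3.
- Place 4: 1.
- Mean: (0.500 + 0.667 + 0.667 + 1)/4 = 70.8%, against 50% with no information.

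**Alternatives.** Fixed blocks of 6 and 8 were enumerated. Randomly varying sizes were simulated with two strata of 40 and an observer who knows which sizes are in use, but not their order, and updates by Bayes' rule.

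| Design | Certain | Best guess right |
|---|---|---|
| Fixed 4 (plan) | 33.3% | 70.8% |
| Fixed 6 | 25% | 68.3% |
| Fixed 8 | 20% | 66.6% |
| Random 4/6 | about 6% | about 69% |
| Random 4/6/8 | about 2 to 3% | about 68% |
| Patient-specific pack codes | 0% | 50% |

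The last row follows by reasoning: if the earlier allocations cannot be read, nothing can be counted. Varying the block size removes most of the certainty but little of the guessing advantage (71% to 68%). Removing the two-letter label removes both.

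**The case against.** The strongest reply is that the calculation rests on an observer whom the article does not describe. It does not say who hands out, takes back or counts the packs, or that recruiters see the letters. An independent coordinator assigns, and "A person not involved in the study will randomly divide patients into two groups: intervention (inulin, *n* = 40) and control (placebo, *n* = 40". The Discussion gives weekly contact to a project coordinator. A recruiter would have to see all earlier letters, keep them in order by stratum and know the block size. Age 35 falls in both strata as written, which blurs the count. What becomes predictable is a letter, not a treatment, and the packs look alike.

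Most of this stands, and it makes the point conditional. It does not remove it. The safeguards described protect the next envelope and the meaning of A and B. Nothing in the article says that the letters are kept from those who recruit, and those people also treat and follow up. Selecting by letter can unbalance the arms even when nobody knows which letter is inulin. The step from letter to treatment is also short: Data management {19} allows unblinding after an adverse event, and with two codes one such event decodes every woman whose letter is known.

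It might also be said that role detail belongs in a fuller document. That is fair for who handles packs, but the block size and the two-letter labels are choices that the article itself fixes.

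**Conclusion.** The point holds as a conditional weakness that is cheap to remove. About one third of letters (25 to 27 of 80) are certain, and about 71% can be guessed correctly, for anyone who knows the earlier letters and strata. The arithmetic is exact under that assumption. That recruiting staff are such observers is an inference from their combined roles and the pack handling. The resulting bias in headache frequency cannot be sized from the document.

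Three stronger readings are tempting and not supported:
- A reader might infer that concealment fails. The article shows only that it can be defeated, and directing women towards inulin needs the A/B code to be guessed or broken as well.
- A reader might infer that the block size was public during recruitment. The article gives a version date (September 17, 2023) inside the recruitment window (August 21, 2023 to March 22, 2024), but no publication date.
- A reader might take the statement that "The generation of the allocation sequence for patients will be monitored by a second researcher" as a further leak. Nothing says that this person sees the list during recruitment, or recruits or assesses patients, so that would be an argument from silence.

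**What to change.** 1. In Sequence generation {16a}, generate the unused part of each stratum's list, from the next unopened block, with randomly varying block sizes (for example 4, 6 and 8). Do not disclose the sizes to recruiting staff until enrolment ends. The amendments section {25} has changes reported in detail on the registry, so the public entry should say only that sizes vary and are withheld.
2. Preferably also, in Intervention description {11a} and Concealment mechanism {16b}, replace A and B on the remaining packs with patient-specific codes. This does more than step 1, because it removes the information on which the prediction depends. It also limits any single unblinding to one woman among those so labelled.

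The cost is re-preparing the unused envelopes and labels. The possible end-of-trial imbalance rises from 2 to 4 per stratum, that is, half of the largest block (4/2 = 2; 8/2 = 4). The figures for varying sizes apply only to women randomised after the change; those already enrolled stay under the fixed block of four.
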